### Interim analyses {21b}

There are no anticipated harmful consequences or real risks for the participants involved in this intervention. Thus, interim analyses, discontinuation rules, or criteria for discontinuing or modifying allocated interventions will not be included in the current protocol. Furthermore, all participants will be aware of their voluntary participation and therefore will be informed that they can withdraw from the program at any time.

### Methods for additional analyses (e.g., subgroup analyses) {20b}

An additional analysis will be performed with the subgroup of patients who were infected with SARS-COV-19 during their participation in the study.

### Methods in analysis to handle protocol non-adherence and any statistical methods to handle missing data {20c}

Before the start of the registration of participants, training will be carried out to instruct all researchers in the collection and entry of data and in the implementation of interventions. Timely data entry will allow early detection of problems with missing data (forgetting, overlapping crosses). In order to detect them, a verification process will be implemented for all questionnaires after completion and for all variables after entering the SPSS database.

### Plans to give access to the full protocol, participant-level data, and statistical code {31c}

We will provide the protocol, participant-level data, and statistical code upon request.

## Oversight and monitoring

### Composition of the coordinating center and trial steering committee {5d}

This study does not have a designated coordinating center or study steering committee. The study is a single center and the research team at the hospital where the study will be carried out will be responsible for conducting and monitoring the daily tasks necessary for the execution of the study. This team meets periodically to assess the conduct and progress of this study and ensure compliance with the study protocol. There are also meetings every 3 months with those responsible for coordinating the study (principal investigator (PI) and co-investigator (Co-PI)) to discuss management and financial issues related to the study. To ensure that the protocol is implemented as planned, the PI will be responsible for managing and overseeing the study and providing guidance and administrative support. Weekly, the research assistants will meet to establish short-term objectives, consult the fulfillment of previously established goals, and identify problems or deviations from the plan.

### Composition of the data monitoring committee, its role, and reporting structure {21a}

It will not be necessary to form a data monitoring committee (DMC) to independently assess the safety, scientific validity, and integrity of the clinical trial because this intervention is a low-risk intervention, does not present substantial safety issues, and does not have a double-blind treatment.

### Adverse event reporting and harms {22}

The present intervention carries minimal risks, so we do not expect any serious or severe adverse events. However, over time participants will be contacted and asked about their physical and mental well-being. In addition, participants will have access to a 24-h telephone contact that they can call if needed. If a serious or severe adverse event occurs, the Ethics Committee will be notified.

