**Methods:**

This is a single-center, prospective, three-arm, single-blind, randomized, controlled, superior clinical trial with stratified and blocked random allocation. Three hundred participants with PAD and IC will be recruited from an Angiology and Vascular Surgery Department, Centro Hospitalar Universitário Porto (CHUPorto), Porto, Portugal. All patients will receive the same medical care recommended by  current guidelines. Participants in all three groups will receive a personalized prescription for an HBET program and a behavioral change and motivational intervention. Participants in experimental groups 1 and 2 will receive a smartphone with the WalkingPad app to monitor exercise sessions. Experimental group 2 WalkingPad app will have a built-in virtual assistant that will promote behavioral change and provide motivational support. Participants allocated to the active control group will not receive the m-health tool, but a practice diary to encourage monitoring. The  program will last for 6 months with three evaluation moments (baseline, 3, and 6 months). The primary outcome will be the change in distances walked (maximal and pain-free) from baseline to 3 and 6 months. Secondary outcomes will be changes in quality of life, patients’ perception of resistance, and walking speed.

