## Introduction

### Background and rationale {6a}

Cardiovascular (CV) disease remains the leading cause of death worldwide with the 2013 Global Burden of Disease study estimating that it accounted for 31.5% of all deaths globally [1], representing a considerable economic burden to society and healthcare systems. Lower extremity peripheral artery disease (PAD) is a common cardiovascular disease that affects 27 million people in Europe and the USA. Intermittent claudication (IC) is usually the first symptom of PAD, resulting in walking impairment due to muscle ischemia. IC is defined as fatigue, discomfort, cramping, or pain of vascular origin in the muscles of the lower extremities that is consistently induced by exercise (same distance) and consistently relieved by rest [2]. Severity is generally described in terms of claudication distance, and it can be objectively measured by treadmill test with the assessment of pain-free walking distance (PFWD), maximal walking distance (MWD), and functional walking distance (FWD). However, recent evidence states that the 6-min walk test assessed in a 30-m walkway is a more valuable measure as it is more representative of daily life walking [3]. Furthermore, the discomfort related to IC contributes to a sedentary lifestyle, decreasing physical fitness level, enhancing cardiovascular risk factors, and increasing rates of mobility loss, thus leading to disease deterioration. Hence, the significant functional decline in patients with PAD is associated with the severity of IC, which, in turn, is correlated with higher morbidity, reduced quality of life (QoL), and increased mortality [4–6].

Thus, exercise therapy programs have been recommended as first-line therapy for patients with PAD and IC [7], improving walking ability, functional status, and health-related QoL. Data from randomized clinical trials suggests that exercise therapy is the best initial treatment for IC and show improvements in PFWD and overall walking performance [8, 9]. Regular aerobic exercise also reduces cardiovascular risk and increases the event-free survival rate from 57 to 81% in patients with PAD [10]. In addition, walking distance can decrease by 8.4 m per year after the onset of IC [11]. Therefore, exercise therapy can break this cycle and even reverse it, being an effective, low-cost, and low-risk option compared to more invasive therapies for IC.

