### Sample size {14}

The sample size was calculated for an effect size of 0.25, a statistical power of 80%, and a significance level of 5%; á priori 57 participants will be needed in each of the groups (G*Power software, version 3.1.9). This calculus was based on previous studies (*F* tests, ANOVA: repeated measures, within-between interaction) [15, 17]. The calculated sample size is expected to be reached by the end of May 2022.

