**Fig. 2 Fig2:**
[figure not shown]
Flow diagram of the clinical trial

The primary outcomes will be measured by two tests. The walking distance measured with a standardized treadmill test [34, 35] is a widely used tool for functional assessment and monitoring of exercise rehabilitation, where PFWD, FWD, and MWD are objective measures of improvement. In turn, the 6MWT is an individualized test that assesses the submaximal level of functional capacity [35, 38]. The patient chooses the intensity of the exercise and can rest during the test, which better reflects the functional level of exercise practiced in daily physical activities. Therefore, we chose to use both measures (walking distance measured with the treadmill test and walking distance measured with the 6MWT) not only because they complement each other but also because both provide different and valuable information.

The primary outcomes will reflect the effectiveness (beneficial effect) and not the harm (adverse effect) of the intervention. The change achieved in primary outcomes from baseline to 3 and 6 months will be a valid, reproducible, and relevant result for the target population and healthcare professionals. The amount of change achieved will be represented in a continuous variable that will facilitate comparisons and grouping of results across studies, trials, and meta-analyses. Data collection forms can be requested from the responsible investigator.

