## Discussion

PAD represents a considerable economic burden for society and health systems, for patients and families, and therefore, cost-effective treatments are necessary. As SET programs are difficult to implement systematically in all patients whenever needed, new options must emerge, and research has shown that HBET programs are more accessible, effective, appropriate, cheaper, patient-friendly, and enjoyable (in contact with nature) to control IC in patients with PAD. M-health tools are a promising adjuvant strategy as they are practical, easy to use, and cost-free. Virtual assistants have been successfully used to promote adherence to self-care in various chronic diseases but have not yet been used to promote the practice of physical exercise in patients with PAD. Thus, to the best of our knowledge, this will be the first randomized clinical trial evaluating the effectiveness of an HBET program with a behavioral change and motivational intervention delivered by a virtual assistant, to promote adherence to physical exercise and, consequently, improve walking distances in patients with PAD and IC.

The main limitation of this study refers to the low digital literacy of this population. The inclusion of participants regardless of their level of digital literacy, access to digital devices and to Internet, is likely to be a factor influencing the results. However, the goal is to make an app available to the entire population of people with PAD and not just to the youngest and most digitally literate.

The strengths of this study include that participation requires no more consultations than previously scheduled, no engagement with healthcare professionals or researchers (apart from formal study assessments), and interventions do not have serious effects on individuals when exclusion criteria are assured. Communication with the research assistant will be facilitated with an email address and a phone number. Furthermore, as almost all (if not all) individuals use cell phones, these m-health tools and virtual health assistants can potentially fill a gap in access and quality of healthcare services and information available, reducing the burden on the health system and promoting self-management  and self-care in chronic illness.

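### Low intervention risk does not justify expecting no serious adverse event of any cause, and the harm ascertainment described is unstructured and possibly unequal between arms

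*Protocol article*

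**What the plan says.** In the protocol article, Adverse event reporting and harms {22} states: "The present intervention carries minimal risks, so we do not expect any serious or severe adverse events". It then says that participants will be asked over time how they are, physically and mentally, that they can ring a 24-hour number, and that the ethics committee will be told of any serious or severe event.

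Other sections bear on harm:

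- Plans for assessment and collection of outcomes {18a}: "The primary outcomes will reflect the effectiveness (beneficial effect) and not the harm (adverse effect) of the intervention". Outcomes {12} lists walking distances, quality of life, perceived walking ability, process variables and descriptive data, and no adverse-event outcome. Statistical methods {20a} describes no comparison of events by arm.
- Interim analyses {21b} and the data monitoring committee item {21a} rest on the same low-risk premise.
- Criteria for discontinuing {11b} names worsening symptoms as a reason to discontinue and has reasons for withdrawal recorded where possible. The retention item {18b} offers the 24-hour number for adverse events.
- Intervention description {11a}: the active control group and experimental group 1 (ExpG1) have psychologist sessions and telephone calls. Experimental group 2 (ExpG2) has the virtual assistant instead, with neither in-person nor telephone contact.
- The Discussion counts as a strength that "interventions do not have serious effects on individuals when exclusion criteria are assured". It also says that participants need no dealings with clinicians or researchers outside the study assessments.
- Background and rationale {6a} says that regular aerobic exercise "increases the event-free survival rate from 57 to 81% in patients with PAD", and links the severity of claudication to morbidity and mortality.

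**The concern.** An adverse event is ordinarily recorded whether or not the intervention caused it. The step from a low-risk intervention to no serious event at all therefore skips background events, which the Background itself leads one to expect in this disease.

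The consequence lies in ascertainment. A plan that expects nothing has little reason to specify how events are sought, and this one names an open question on well-being and a telephone line that the participant has to use. If the open question is put during intervention calls, ExpG2 will be asked less often than the other two arms. That is the arm in which human support was replaced by software. Fewer recorded events there could reflect less asking rather than fewer events. The trial compares three ways of supporting unsupervised walking to near-maximal pain. As described, it could report which arm walks further, but not on an equal footing whether falls, cardiac events or limb events differed.

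**Working it through.** The plan's figure is qualitative (no events expected) and has no rate behind it, so there is no calculation to reproduce. The check asks whether none is a reasonable all-cause expectation given the percentages that the article cites.

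**Inputs from the article**

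- Event-free survival S = 0.57 without and 0.81 with regular exercise (Background {6a}). Neither a time horizon nor an event definition is given.
- Number of patients: the Abstract says "Three hundred participants with PAD and IC will be recruited", while Sample size {14} says "57 participants will be needed in each of the groups", that is 3 × 57 = 171. Both are used.
- Follow-up: 6 months, or 0.5 year (Abstract, Methods).

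**Assumptions, not in the article**

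- The percentages refer to a horizon T of 1 to 10 years.
- The hazard is constant.

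**Formula.** 6-month risk p = 1 − S^(0.5/T); expected patients with an event = N × p. For example, with S = 0.81 and T = 5, p = 1 − 0.81^0.1 = 0.0209, and 300 × 0.0209 = 6.3.

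| T (years) | p at 81% | p at 57% | N = 300, 81% | N = 300, 57% | N = 171, 81% | N = 171, 57% |
|---|---|---|---|---|---|---|
| 1 | 10.00% | 24.50% | 30.0 | 73.5 | 17.1 | 41.9 |
| 3 | 3.45% | 8.94% | 10.4 | 26.8 | 5.9 | 15.3 |
| 5 | 2.09% | 5.47% | 6.3 | 16.4 | 3.6 | 9.3 |
| 10 | 1.05% | 2.77% | 3.1 | 8.3 | 1.8 | 4.7 |

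All three arms are prescribed walking, so the 81% columns are the more relevant if patients adhere; the 57% columns mark the upper end.

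**How long a horizon would make none plausible?** Setting N × p = 1 gives T = 0.5 × ln S / ln(1 − 1/N). At 81% this is about 31.6 years for N = 300 and 18.0 years for N = 171. The probability of no event at all, (1 − p)^N, at 81% and T = 10 is 4.2% for N = 300 and 16.5% for N = 171.

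**What would zero observed events show?** The one-sided 95% upper limit is 1 − 0.05^(1/n): 1.0% for n = 300, 1.7% for n = 171, 3.0% for 100 per arm and 5.1% for 57 per arm. These limits also assume that every event was found.

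**Statements on contact, side by side**

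- Harms {22}: participants will be contacted over time, with no arm, interval or mode named.
- Adherence strategies {11c}: reinforcement calls are listed without restriction to an arm.
- Intervention description {11a}: ExpG2 has no in-person or telephone contact.
- Discussion: no dealings with researchers apart from the assessments.

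These cannot all hold for every arm as written. The assessments at 3 and 6 months (t2, t3) are the only contact that all of them leave in place for all three arms.

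**The case against.** The strongest reply is that the harms sentence argues from the intervention and so means related events only; background cardiovascular events would not contradict it. The text then provides for the case that an event does occur. That reading is possible, but the sentence makes no such distinction and the notification rule covers serious events regardless of cause. The wording should settle the matter.

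A reader might infer that the article's own survival figures imply several serious events and so contradict the plan. The article does not support that. The figures have no horizon and no event definition, and an event in the cited source need not be a serious adverse event here. The range spans more than 20-fold, almost all of it from the assumed horizon and the choice between 57% and 81%. With 171 patients, 81% and 10 years, the expected count is 1.8. Eligibility {10} also excludes recent infarction or unstable angina, severe heart failure, severe lung disease, active cancer and critical ischaemia, which would lower the rate.

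A reader might also infer that harm goes uncollected, or that an ethics notice is all that ever happens to an event. That is not so: the well-being contact, the 24-hour line and the recorded reasons for withdrawal are all stated, and {30} provides for referral after the trial. The sentence in {18a} concerns the primary outcomes only.

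Finally, an article may leave adverse-event forms and tables to a fuller document, and their absence alone would be no finding. The point rests instead on what the article does state: an expectation that does not follow, and contact arrangements that disagree. The Discussion sentence is best read as a premise about the intervention, not as a promised result.

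**Conclusion.** The point holds in a limited form. Expecting no serious adverse event of any cause does not follow from low intervention risk. Under assumed horizons of 1 to 10 years and constant hazard, the cited percentages correspond to 3.1 to 73.5 patients with a background event among 300, or 1.8 to 41.9 among 171, in 6 months, before the exclusions are taken into account. These numbers show only that none is a poor all-cause expectation; they are not a forecast.

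The more practical weakness is ascertainment. What is described is unstructured, and the article contradicts itself on who is contacted. Unequal recording between arms is a risk, not an established fact: it depends on whether the well-being contact follows the intervention calls. The safety premise in the Discussion has no described comparison behind it, and even zero events would leave an upper limit of 3.0% with 100 per arm or 5.1% with 57 per arm.

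**What to change.** 1. Reword {22} to say that no serious events related to the intervention are expected, while background events in this population are. Do not insert a count, because the cited figures are undated.
2. Reconcile {11a}, {11c}, {22} and the Discussion on who is contacted between assessments and how.
3. At t2 and t3, ask all three arms the same short list, for example death or hospital admission (from records), cardiac event, limb event, and fall or injury while walking.
4. Tabulate serious and non-serious events descriptively by randomised arm.
5. Make the Discussion's safety statement conditional on that table, or delete it.

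The cost is a few minutes at two existing visits, one form page and one table, with no extra visits or staff. Recruitment had already begun, so anyone past t2 would have to be asked at t3 about the whole period. With few events, the table can describe the arms but cannot establish that they differ.

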### Frequency and plans for auditing trial conduct {23}

The need for an audit is not foreseen; however, the training and research center of the hospital where the study will be carried out may audit the study.

### Plans for communicating important protocol amendments to relevant parties (e.g., trial participants, ethical committees) {25}

Changes in the study protocol will first be submitted to the Ethics Committee of the Hospital where the study will be carried out and, after approval, updated accordingly on the clinical trials website.

## Dissemination plans {31a}

The WalkingPad program results dissemination plan includes (1) writing and publishing articles in indexed journals, including the WalkingPad protocol and the article on the effectiveness of the intervention program and the set of variables that contribute to adherence to physical exercise in the long term; (2) present the results of the study to health professionals at scientific conferences and events; (3) disseminate the study results to the participants through a social event organized at the end of the study; (4) share the results with the public and other relevant groups, via the media (TV and newspapers) and social networks (Facebook, Instagram, and Twitter); (5) update the WalkingPad project website with pertinent information [5]; systematize guidelines on m-health interventions to increase the effectiveness of HBET programs not only in PAD but also in cardiovascular disease in general.

## Discussion

PAD represents a considerable economic burden for society and health systems, for patients and families, and therefore, cost-effective treatments are necessary. As SET programs are difficult to implement systematically in all patients whenever needed, new options must emerge, and research has shown that HBET programs are more accessible, effective, appropriate, cheaper, patient-friendly, and enjoyable (in contact with nature) to control IC in patients with PAD. M-health tools are a promising adjuvant strategy as they are practical, easy to use, and cost-free. Virtual assistants have been successfully used to promote adherence to self-care in various chronic diseases but have not yet been used to promote the practice of physical exercise in patients with PAD. Thus, to the best of our knowledge, this will be the first randomized clinical trial evaluating the effectiveness of an HBET program with a behavioral change and motivational intervention delivered by a virtual assistant, to promote adherence to physical exercise and, consequently, improve walking distances in patients with PAD and IC.

The main limitation of this study refers to the low digital literacy of this population. The inclusion of participants regardless of their level of digital literacy, access to digital devices and to Internet, is likely to be a factor influencing the results. However, the goal is to make an app available to the entire population of people with PAD and not just to the youngest and most digitally literate.

The strengths of this study include that participation requires no more consultations than previously scheduled, no engagement with healthcare professionals or researchers (apart from formal study assessments), and interventions do not have serious effects on individuals when exclusion criteria are assured. Communication with the research assistant will be facilitated with an email address and a phone number. Furthermore, as almost all (if not all) individuals use cell phones, these m-health tools and virtual health assistants can potentially fill a gap in access and quality of healthcare services and information available, reducing the burden on the health system and promoting self-management  and self-care in chronic illness.

